**10. Direct access to source data/documents**

The investigator/institution involved in the study must ensure direct access to source data/documents by the monitor, the auditor, the LEC/IRB or regulatory authorities.

## **11. Quality control and quality assurance**

### ***11.1. Data quality assurance***

According to the ICH GCP and regulatory requirements, the Sponsor, a third party on its behalf, regulatory authorities, or local ethics committees can perform audits (inspections) to assure quality any time during the study or after its completion. The investigator must give the auditor/inspector direct access to all study documents (including source documents) and discuss (personally, or designate someone from the study team) the audit/inspection results and other matters with the auditor/inspector.

### ***11.2. Investigator's adherence to the Protocol***

Before beginning the study, the investigator must read and accept all provisions of this Protocol. The investigator must conduct the study in accordance with this Protocol, the ICH GCP, and other regulatory requirements of participating countries.

No protocol deviations are allowed during the study without a previous written approval from JSC BIOCAD, the Ministry of Healthcare of the Russian Federation and Local Ethics Committees, except for the cases when the deviation is necessary to protect a patient from an immediate hazard.

The investigator should have enough time to accurately perform and complete the study within the timeframes specified by JSC BIOCAD, enough employees of appropriate qualification, and adequate equipment to conduct the study according to the Protocol.

Each sub-investigator participating in the study must read the Protocol and be aware of his/her responsibilities/functions in the study. If the principal investigator delegates some of his/her functions to sub-investigators, this must be documented in a relevant section of the Investigator's File.

### ***11.3. Investigator's responsibility to comply with the Protocol***

At each study site, the decision regarding patient's early withdrawal from the study has to be approved by JSC BIOCAD.

If the investigator decides to withdraw a patient from the study, he/she must send a request, specifying a reason for withdrawal, to BIOCAD's Medical Advisory Division by [contact]. Within 48 hours (except for weekends and public holidays) from the time when the request was received by the Medical Advisory Department, JSC BIOCAD should notify the investigator of the decision regarding patient withdrawal. If a patient has to be immediately withdrawn from the study due to an SAE, the investigator must inform JSC BIOCAD about the SAE within 24 hours but does not have to wait for approval from JSC BIOCAD.

If a subject does not attend a scheduled visit or makes unauthorized changes in the dose of the investigational product, the investigator must report the violation to the Medical Advisory Division

of JSC BIOCAD within 24 hours from the time of awareness (by fax: [name]). Medical advisors will instruct the investigator on further case management and on how to document the causes of the violations in the CRF/source documents.

If the investigator fails to follow these procedures or if multiple Protocol violations occur, JSC BIOCAD may suspend or terminate the study at this particular study site.

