#### ***4.8.2. Criteria for premature withdrawal of study subjects***

The patient will be withdrawn from the study in the following circumstances:

1. A major violation of inclusion/exclusion criteria is revealed after the patient was enrolled in the study (withdrawn by the decision of JSC BIOCAD).
2. The patient recalls his/her consent to participate in the study.
3. The patient develops adverse events or serious adverse events, laboratory abnormalities or comorbidities that, in the investigator's opinion, make further participation in the study

---

 Deviations from inclusion/exclusion criteria justified by the investigator and approved by the Sponsor are not considered a reason for withdrawal.

impossible, dangerous or non-beneficial regarding patient's well-being and/or safety.

4. The patient misses more than 4 injections and/or visits during the study (compliance < 85%) or misses 2 consecutive injections and/or visits, or breaches the specified time windows for more than 5 visits.
5. The patient develops active tuberculosis. If the patient has indeterminant or positive results of the QuantiFERON assay or T-Spot.TB or Diaskintest® at Week 25, he/she can continue the study only if all three of the following requirements are met:
  - The patient tests negative in one additional QuantiFERON / T-Spot.TB assay.
  - The chest X-ray shows no signs of active tuberculosis.
  - The TB specialist confirms that the patient has no tuberculosis.Otherwise, the patient has to be removed from the study.
6. The patient gets pregnant. If pregnancy is suspected, the urine test for HCG must be performed. If the test gives a positive result, the patient must be withdrawn from the study (follow-up procedures are described in section 5.4).
7. The patient has a major depressive disorder or suicidal ideation or makes suicidal attempts.
8. The study is terminated by JSC BIOCAD, local ethics committees, or regulatory authorities.
9. The patient uses medications prohibited by the Protocol.
10. The patient dies.

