***The investigator must inform JSC BIOCAD within 24 h about a patient's premature withdrawal and specify the reason.***

If the subject discontinues the study, an Early Withdrawal Form should be filled out in the CRF. The follow-up procedures for the discontinued subjects are described in section 5.4 *Procedures by Visits*.

Patients who discontinued the study due to safety-related reasons will not be replaced.

For further details, refer to section 11.5 *Study termination*.

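### Section 11.3 puts every early withdrawal to the sponsor for approval, and its SAE-only waiver is too narrow for pregnancy, non-serious adverse events, recalled consent and therapy needed under 6.2.2

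*Protocol*

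**What the plan says.** Section 11.3 opens with a general rule: "At each study site, the decision regarding patient's early withdrawal from the study has to be approved by JSC BIOCAD". When the investigator decides to withdraw a patient, a request with the reason goes to the sponsor's medical advisory group. The answer is more than an acknowledgement: "JSC BIOCAD should notify the investigator of the decision regarding patient withdrawal". Its deadline is 48 hours from receipt, and weekends and public holidays are not counted. One situation is released from waiting: "If a patient has to be immediately withdrawn from the study due to an SAE", the investigator reports the event within 24 hours and need not await approval. The procedure carries a sanction: "If the investigator fails to follow these procedures or if multiple Protocol violations occur, JSC BIOCAD may suspend or terminate the study" at that site.

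Sections 4.8.2 and 5.3 list the same ten grounds on which a patient will be withdrawn. They include recalled consent (item 2), adverse events whether or not serious when the investigator judges further participation impossible, dangerous or of no benefit (item 3), and pregnancy (item 6), where "If the test gives a positive result, the patient must be withdrawn from the study". Both lists end with a notice rule: "The investigator must inform JSC BIOCAD within 24 h about a patient's premature withdrawal and specify the reason". Only item 1, a major eligibility violation, names the sponsor as the one who decides.

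Section 6.2.2 adds that a patient who needs a prohibited treatment must leave the study before that treatment begins.

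**The concern.** The general rule in 11.3 and the mandatory grounds in 4.8.2 and 5.3 do not fit together. If the protocol has already fixed that a patient must leave, sponsor approval has nothing left to settle. If the patient has recalled consent, the decision is not the sponsor's to approve. The single waiver is tied to seriousness, but two of the mandatory grounds are not confined to serious events.

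Two things are at stake. The first is clarity about who decides: a site that follows 11.3 literally submits a recalled consent or a pregnancy withdrawal for approval, under a procedure whose breach can lead to suspension of the site. The second is time to treatment. Under 6.2.2, phototherapy or a systemic agent cannot start until the patient is out of the study, so the reply time can become a treatment delay.

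**Working it through.** **Step 1. Which of the ten grounds does the waiver miss?** The table sets the items of 4.8.2 and 5.3 against 11.3.

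| Item | Ground | Position under 11.3 |
|---|---|---|
| 1 | Eligibility violation | Sponsor decision is written into the item; no misfit |
| 2 | Recalled consent | Caught by the opening sentence only; misfit |
| 3 | Adverse event, serious or not | Waiver covers SAEs only; misfit when not serious |
| 4 | Missed injections or visits | 11.3 itself foresees a sponsor role: "Medical advisors will instruct the investigator on further case management"; no misfit |
| 5 | Active tuberculosis | Not named in the waiver; no separate misfit shown |
| 6 | Pregnancy | Withdrawal mandatory and not an SAE under 8.1.1.2; misfit |
| 7 | Major depression, suicidality | Not named in the waiver; no separate misfit shown |
| 8 | Study terminated | No site decision |
| 9 | Prohibited drug used | Drug already in use; nothing waits |
| 10 | Death | No decision |

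Count: 2 suited to sponsor review (1, 4) + 2 with no site decision (8, 10) + 1 with the drug already in use (9) + 5 others (2, 3, 5, 6, 7) = 10. Of those five, three are clear misfits (2, 6, and 3 when the event is not serious).

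**Step 2. Does pregnancy fall under the SAE waiver?** Section 8.1.1.2 lists use of the product in pregnancy among information that is reported and followed up like an SAE but is expressly not one. On the text, the waiver does not reach it.

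**Step 3. Can therapy be held up?** Section 6.2.2 makes withdrawal a precondition for prohibited therapy, and 11.3 makes withdrawal depend on approval. Starting earlier would be use of a prohibited drug (item 9). Section 11.2 allows departures without prior written approval only to avert an immediate hazard. For non-emergency therapy the wait therefore runs until the sponsor replies.

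**Step 4. How long at most?** The input is the 48-hour limit in 11.3. Assumptions: the weekend is Saturday and Sunday, and the clock runs round the clock on all other days.

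- Monday 09:00: 15 h Monday + 24 h Tuesday + 9 h Wednesday = 48 counted hours, ending Wednesday 09:00. Calendar time is 48 h, which is the protocol's own figure.
- Friday 18:00: 6 h Friday + 24 h Monday + 18 h Tuesday = 48 counted hours, ending Tuesday 18:00. Calendar time is 4 × 24 = 96 h.
- Friday 18:00 with Monday a public holiday: 6 h Friday + 24 h Tuesday + 18 h Wednesday = 48 counted hours, ending Wednesday 18:00. Calendar time is 5 × 24 = 120 h.

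Running the same clock for every quarter-hour of a holiday-free week gives a latest reply of 48 h for requests received Monday to Wednesday, 48 to 96 h on Thursday, 96 h on Friday, 72 to 96 h on Saturday and 48 to 72 h on Sunday.

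**The case against.** The strongest reply is that little actually waits.

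- Stopping study drug is separate from leaving the study (Terms and definitions) and is the investigator's call (6.1.3.1). In confirmed pregnancy it must happen at once (8.1.1.2).
- Any treatment that is not prohibited may be given, including topical glucocorticoids (6.2.1). Single emergency doses of systemic glucocorticoids are allowed (footnote to 6.2.2), and immediate hazards are exempt (11.2).
- The request step in 11.3 is triggered by an investigator's decision, which recalled consent is not. Section 13.2 lets a patient's recall of data authorization take effect with no sponsor role.
- Sponsor review has a purpose: dropouts for reasons other than safety may be replaced before Week 16 at the sponsor's discretion (4.2), so the reason for withdrawal matters.

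All of this is accepted, and it limits the point. It does not remove it. The opening sentence of 11.3 has no exception for recalled consent, and 13.2 concerns data, not participation. Stopping the drug does not satisfy 6.2.2, which asks for withdrawal from the study. The sponsor's interest in the reason is met by the 24-hour notice.

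A reader might go further in three ways that the text does not support.

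- One might infer that 4.8.2 and 5.3 flatly contradict 11.3 by asking for notice alone. They do not say that notice is enough, and one message within 24 hours can serve as both notice and request.
- One might infer that a patient who recalls consent, or is pregnant, is kept on treatment until approval. Nothing in the protocol says so.
- One might read 48 to 96 hours as the delay. It is the range of the latest permitted replies in a week without holidays, and the sponsor may answer the same day.

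**Conclusion.** The point holds and is minor. Read literally, 11.3 submits to sponsor approval two kinds of withdrawal that the protocol itself mandates (non-serious adverse events under item 3, and pregnancy) and, through its opening sentence only, the patient's own recall of consent. The one practical consequence is a possible delay to non-emergency prohibited therapy under 6.2.2. It is bounded at 48 h on weekdays, 96 h over a weekend and 120 h with one adjoining public holiday. The bounds rest on the clock assumptions stated with the calculation. Two adjoining holidays would give 144 h.

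Drug exposure, emergency care and the Week 16 PASI 75 analysis are not affected. Three neighbouring rules are not part of the point: withdrawal for missed visits, withdrawal after a prohibited drug has already been used, and the 14-day interruption rule in 6.1.3.2 and 6.1.3.3, which has its own exception decided by the investigator and the monitor.

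**What to change.** Reword section 11.3 in four places:

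1. State that recalled consent takes effect without sponsor approval.
2. Extend the no-wait waiver, with notice and reason within 24 hours, to all item 3 withdrawals whether or not serious, and to pregnancy.
3. Apply the same waiver to withdrawals needed to start therapy under 6.2.2, so that treatment may begin once the investigator has withdrawn the patient and notified the sponsor.
4. Keep prior sponsor review for eligibility violations, non-compliance and reasons not on the list.

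For consistency the same wording may cover active tuberculosis and depression or suicidality, although neither was shown to be a misfit in its own right.

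The cost is the text of one section. The sponsor gives up prior review of the reason in these cases but still learns it within 24 hours, in time to decide on replacement before Week 16. No withdrawal criterion, endpoint or analysis changes.

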#### ***11.4. Study monitoring***

Before the study beginning (at the Study Initiation Visit or investigators' meeting), a representative (CRA) of JSC BIOCAD (or an authorized CRO) will explain the Protocol and the CRF to the investigators and members of the study teams. During the study, the CRA will regularly visit the study site to check the completeness of patient records, accuracy of information in the CRF, adherence to the Protocol and GCP, process of patients' recruitment, and storage, dispensing, and accounting of the investigational products according to applicable requirements. During these visits, key members of the study team should be available to assist the CRA and resolve arising issues (if any).

Study monitoring is performed according to appropriate SOPs of JSC BIOCAD.

For each study subject, the investigator should keep source documents containing the subject data and records made during visits (medical records of the study center), including demographics, medical information, laboratory findings, ECG, and all other tests or examinations. Any information contained in the CRF should be also recorded in the patient's source documents. The investigator must keep the original ICF. A copy of the signed ICF will be given to the patient.

The investigator should provide the CRA with all relevant patient source documents to confirm that data in the source documents is consistent with the data in the CRF. The investigator should ensure the timely completeness of the CRFs before the CRA's visit.

The CRA will check the CRFs and other study materials comparing them against the source data to confirm that the study complies with the Declaration of Helsinki, the ICH GCP, regulatory requirements of participating countries, and the Study Protocol, and to confirm the authenticity, accuracy, and completeness of data.

Upon the study completion, a representative of JSC BIOCAD (CRA) should visit the study site to perform the study closeout visit. During this visit, the Sponsor's representative will collect all necessary documentation in accordance with the SOP of JSC BIOCAD.

#### ***11.5. Data management and quality control***

In the trials that involve eCRFs, JSC BIOCAD employees (or employees of an authorized CRO) will check the data entered by the study team members for accuracy and completeness. If there are

any inconsistent or missing data points, queries will be generated with a request for clarification. All queries are sent to the study site. A designated member of the study team must immediately answer the request and make all required changes to the database.

At the end of the study, any protocol deviations will be determined. After clarifying protocol deviations and confirming the completeness and accuracy of the data, the database is locked, the blind codes are opened, and the data are ready for analysis.

#### ***11.6. Study termination***

JSC BIOCAD can suspend or terminate the study due to safety or ethical issues, Protocol compliance issues, or due other reasons. If JSC BIOCAD suspends or terminates the study, the study site will be notified in advance. In case of suspension or termination, JSC BIOCAD and the investigator have to inform Ethics Committees and regulatory authorities in due time. If the study is suspended or terminated, all study information must be transferred to and all unused investigational product must be returned to JSC BIOCAD.

## **12. Ethics**

### ***12.1. Ethical aspects of the study***

The study will be conducted in compliance with the ethical principles stated in the World Medical Association Declaration of Helsinki (*Recommendations Guiding Physicians in Biomedical Research Involving Human Subjects*, 1964-1996) and the ICH GCP principles.

Before the initiation of the study, the final version of the Protocol (including the Patient Information Sheet and Informed Consent Form) will be submitted for approval to the Ministry of Healthcare of the Russian Federation and the Local Ethics Committees.

All subsequent protocol amendments (other than administrative amendments) must be approved before implementation.

Informed consent must be obtained from patients before starting any study procedures. The Patient Information Sheet contains all the information that a patient may need to make a conscious and independent decision about whether to participate.

During the study, all cases of SAEs will be reported to JSC BIOCAD within 24 hours. JSC BIOCAD will analyze the reports and may suspend the study if considered necessary. Local Ethics Committees will also be notified of all SAEs that are related, in the investigator's opinion, to the investigational product.

All patient personal information is confidential and can be disclosed only if required by law (including court decisions).

All study subjects will be insured. If a subject gets injured directly due to the investigational product, the Sponsor will cover all reasonably justified treatment expenses.

### ***12.2. Confidentiality of study subjects***

The investigator shall protect confidentiality of the trial subjects, the text of this Protocol, and all other study materials and results.

The investigator must ensure subject anonymity. In the CRFs and other documents provided by JSC BIOCAD, patients should be identified by ID codes and/or initials, but never by their names.

The investigator should keep a separate log with Subject IDs, last names, addresses, phone numbers, and medical record numbers (if applicable). The investigator must keep confidentiality of the data not intended for submission to JSC BIOCAD.

All study materials proprietary to JSC BIOCAD cannot be transferred to a third party unless required by the law of the Russian Federation.

### **13. Data handling and record keeping**

#### ***13.1. Record keeping at the study site***

All study documents must be archived at the study site or at the central archive of the institution. A list of all study subject identifiers should be made.

According to the ICH GCP, essential documents include: signed protocol and amendments; copies of completed CRFs; signed ICFs for all patients; medical records; diaries and other source documents; approvals from LECs and regulatory authorities and all correspondence including approved documents; drug accountability records; study correspondence; and the list of patient names and addresses. These are the essential documents that must be kept in the Investigator's File.

The investigator must retain copies of all essential documents for 5 years.

By the end of this period, the Sponsor will inform the investigator(s) about the date when the documents may be destroyed.

Study subject documentation will be archived in accordance with the site in-house SOPs.

The investigator must inform the Sponsor about the place where essential documents are stored and request an approval from JSC BIOCAD before destroying any of essential documents. Appropriate measures must be taken to prevent accidental or premature destruction of these documents.

#### ***13.2. Confidentiality of data***

All information about study subjects will be kept confidential. The information will be processed in compliance with all applicable laws and regulations. These regulations require informing study subjects and obtaining their written authorization regarding the following questions:

- What protected health information will be collected in this study?
- Who will have access to this information and on what grounds?
- Who will use or disclose this information?
- Do study subjects have the right to recall their consent for using their confidential health information?

According to the current regulations, if the patient recalls his/her authorization to collect or use his/her protected health information, the investigator still can use all information obtained before the authorization was withdrawn. If the patient recalls authorization to collect or use his/her protected health information, the investigator should do as much as possible to get patient's permission for collecting at least the safety information (i.e. onset of new or aggravation of existing adverse events) until the scheduled end of the study period.

To prevent unauthorized access to protected subject information, the data management system uses integrated safety elements encrypting all the data when sending them in both directions. The access to the system will be controlled with a sequence of individually assigned identification codes and user passwords. These codes and passwords will be given only to authorized members of the study team who have received a special training.

### ***13.3. Collection of data***

This trial uses an electronic data capture (EDC) system. Designated study team members will enter the data required by the Protocol to eCRFs. The eCRFs have been developed with a validated and safe web-based software. The study team members will get access to the EDC system only after being appropriately trained. An automated validation program inspects the eCRFs for inconsistencies and allows the study team members to change or verify the entered data.

The principal investigator is responsible for completeness and accuracy of all the data entered to the eCRFs and for entering and updating the information in a timely manner.

Members of the study team will collect blood samples for the assessments of PK, immunogenicity, and safety of the investigational products. The samples will be then sent to the Central Laboratory for processing.

